### Statistical consideration and sample size estimation

Three analysis sets are defined: the Intent-to-Treat (ITT) population including all patients who are randomized with study medication assignment designated according to initial randomization, regardless of whether patients receive study medication or receive a different medication from that to which they were randomized. This will be the primary population for evaluating all efficacy endpoints as well as subject characteristics.

The safety population consisting of all patients who received at least one dose of study medication. The per protocol population, consisting of all patients of the ITT population who completed at least one chemotherapy cycle, have at least 2 post-baseline assessments regarding the primary endpoint without pre-specified, selected major protocol deviations thought to impact on efficacy analysis.

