### Study objectives

Primary objective is the comparison of the treatment groups with respect to event-free survival (EFS). EFS is defined as the time from randomization till time to development of an event defined as either an impairment (change from baseline of at least ten points in EORTC QLQ-C30, functional domain total score) or withdrawal due to fulfilling the special defined stopping criteria for chemotherapy as well as PN and Best Supportive Nutritional Care (BSNC) in Arm A or BSNC alone in Arm B or death from any cause (whichever occurs first). Chemotherapy will be continued until individual stop-criteria (disease progression, unacceptable toxicity) are met. This is unaffected by the (dis-) continuation of NI in both study arms. NI in both arms will be stopped when two of the three following criteria are met:

1. weight loss > 2% within the last seven days or caloric intake ≤ 500 kcal expected within the next five days,

2. BIA (Bioimpedance Analysis) defined by phase angle and body cell mass (BCM) with a deterioration > 10% (in both parameters)

3. Prognostic Inflammatory and Nutritional Index (PINI) > 10 (only in subjects with no sign of acute inflammation).

This is unaffected by the (dis-) continuation of chemotherapy.

Secondary objectives are the comparison of the treatment groups with respect to tumour-cachexia, Objective Response Rate (ORR), Time to Progression (TTP), Progression Free Survival (PFS), Overall Survival (OS), Toxicity, time from randomization till time point when stopping criteria are met. Furthermore, the definition and evaluation of a scoring system identifying subject groups who will benefit from second line chemotherapy and/or PN.

Accompanying translational research is focussing mainly on molecular signalling as well as on inflammatory parameters. The available results will be correlated with the clinical parameters.

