### Treatment scheme

After implantation of a catheter patients will be treated as follows:

Both study arms receive a chemotherapy consisting of 2000 mg/m^2^/day 5-FU by IV (24 hours) 200 mg/m^2^/day FA IV (30 min) on day 1, 8, 15 and 22 together with 85 mg/m^2^/day oxaliplatin IV (2 hour) on day 8 and 22. Therapy will be interrupted between days 23 to 42. This cycle will be repeated until any stop-criterion for chemotherapy (disease progression or unacceptable toxicity) is met.

Furthermore, all patients receive nutritional consultation and recommendation by experienced nutritionist contemplated as BSNC.

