### Evaluation, toxicity-based dose adjustment and follow-up

All patients must have appropriate lab and radiographic studies conducted prior to study enrolment to meet eligibility criteria. Lab parameters will be obtained at least weekly and imaging will be performed every seven weeks. The patient will be asked at each visit for any adverse event (AE) as well as concomitant medication and pain medication. Quality of life (QoL) questionnaires (QLQ-C30 and the pancreas specific PAN 26 questionnaire) will be handed out to all patients on day 1 and day 22 of each cycle prior to chemotherapy. Decisions regarding weekly chemotherapy treatment and chemotherapy dose-adjustment will be made using the guidelines below and based on haematological parameters monitored once weekly during chemotherapy. In case of grade 3 or grade 4 haematological toxicities chemotherapy should be held until resolution or until toxicity has resolved or dropped to grade 2. PN will be continued. The procedures for patients with leukocytes between 1.0/l and 1.5/l will be discussed individually in the study group. In case of grade 3 or grade 4 gastrointestinal toxicities (including anorexia, dehydration, nausea/vomiting, diarrhoea, mucositis and bleeding) patients will be considered for periodic outpatient intravenous rehydration with anti-emetics according to conventional practice guidelines. Any grade ≥ 2 neurotoxicity should lead to discontinuation of chemotherapy until recovery to at least grade 1. All uncertain cases of toxicities will be discussed by the study group discretion.

Patients can withdraw from study participation at any time. Patients are taken off the study if unacceptable toxicity appears. Unacceptable toxicity is defined as serious side effect or irreversible grade 4 toxicity, independent whether they are expected or unexpected. After the individual ending of the study subjects will receive the best available medical and nutritional care. Patients will undergo imaging and lab analysis (including tumor marker) quarterly and will be tracked by quarterly phone follow-up until death.

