#### Secondary analyses

A sensitivity analysis will be performed on the primary variable to assess the impact of protocol deviations using the per protocol analysis set.

The hazard ratio and the related 95% confidence interval (CI) for the experimental arm relative to control arm will be estimated by proportional hazard regression with treatment, centre and performance status as covariates.

OS, PFS, and TTP will be analyzed in the same manner as in the primary efficacy endpoint. Estimates of the ORR and 95% CI will be calculated and will be compared between treatment groups using the Cochran-Mantel-Haenszel (CMH) test adjusting by the stratification variables used in the stratified log rank test. For subjects with incomplete follow-up, time to last follow-up date will be used as the censoring time in the analysis of time-to-event data.

Descriptive statistics will be provided for the tumour-cachexia parameters. QoL scales, subscales and single item scores will be summarized by the mean and median for each arm and plotted by time. QoL data will be analysed using ANCOVA techniques. A logistic regression analysis will be carried out to identify relevant prognostic factors.

Incidence rates and 95% CI of Adverse Events (AEs) will be summarized. Subject disposition will be tabulated. Baseline characteristics, concomitant medications, vital signs and PS will be tabulated. Study drug administration and reasons for the deviations from the planned therapy will be tabulated. Summary tables will be prepared to examine the distribution of laboratory measures over time.

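### The per-protocol set drops patients whose EFS event is an early death or chemotherapy stop, so the EFS sensitivity analysis mixes deviations with the removal of early failures (minor)

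*Protocol article*

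**What the plan says.** The section on statistical considerations makes the intention-to-treat (ITT) population primary for all efficacy endpoints. The per-protocol set is the part of it "who completed at least one chemotherapy cycle, have at least 2 post-baseline assessments regarding the primary endpoint", and also free of pre-specified major deviations. So there are three conditions: two on exposure and assessment after randomisation, and one on deviations.

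Secondary analyses gives the purpose of the set: "A sensitivity analysis will be performed on the primary variable to assess the impact of protocol deviations using the per protocol analysis set".

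Three other sections fix the timing:

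- Treatment scheme: doses fall on days 1, 8, 15 and 22, then "Therapy will be interrupted between days 23 to 42", and the cycle repeats until progression or unacceptable toxicity.
- Evaluation and follow-up: the quality-of-life (QoL) forms "will be handed out to all patients on day 1 and day 22 of each cycle prior to chemotherapy". Laboratory values are taken at least weekly and imaging is done every seven weeks.
- Study objectives: EFS runs from randomisation. Its events are death, a QoL deterioration given as a "change from baseline of at least ten points in EORTC QLQ-C30, functional domain total score", and, as the third component, "withdrawal due to fulfilling the special defined stopping criteria for chemotherapy as well as PN and Best Supportive Nutritional Care (BSNC) in Arm A"; the control arm has the matching rule for its own care. The same section says that chemotherapy and the nutritional intervention are stopped independently of each other.

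**The concern.** Early death and stopping chemotherapy under its stop criterion are outcomes that the protocol itself counts in EFS, and neither is a deviation. Both can make it impossible to complete a cycle or reach a second post-baseline assessment. Patients are then left out of the per-protocol set because of the endpoint being analysed, and nothing in the article exempts them.

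What is at stake is the meaning of one named sensitivity analysis. If its result differs from the ITT result, the reader cannot tell whether the cause is protocol deviations or the deletion of early failures. Because EFS is still counted from randomisation, the patients kept carry a stretch of follow-up that was guaranteed free of death and chemotherapy withdrawal. If the treatment works, more controls than experimental patients are removed in this way.

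**Working it through.** **1. When the two conditions can be met.** With dosing to day 22 and a pause on days 23 to 42, a full cycle ends on day 42. The first post-baseline QoL form is on day 22 and the second on day 1 of cycle 2, which is day 43. A lenient reading is possible: a cycle is complete with the day-22 dose, and weekly laboratory or weight checks count as assessments of the primary endpoint. Both conditions could then be met by day 22. If only the first half of that reading holds, the second QoL form still requires day 43.

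**2. Which early events exclude a patient.**

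| Event before day 43 | Excluded by the two conditions? |
|---|---|
| Death | Yes |
| Chemotherapy stopped for toxicity | Yes |
| Chemotherapy stopped for progression | Yes, if found early; with scans every 7 weeks (7 × 7 = 49 days) the first scheduled scan comes after day 43 |
| QoL drop at day 22 | Not by itself; treatment and forms can continue |
| Nutritional stop | Not by itself; chemotherapy continues |

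This takes a chemotherapy stop under its own criterion as an EFS event. If the withdrawal component required the chemotherapy and nutritional criteria together, a chemotherapy stop alone would not be an event, but such a patient would still be excluded without having deviated.

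**3. Reproducing the plan's figures** (Sample size estimation: 4-month EFS 60% and 40%, 36 months of accrual, 4 months of follow-up).

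- HR = ln(0.60)/ln(0.40) = 0.5575 (plan 0.557).
- Schoenfeld, fixed design: 4(1.960 + 0.842)²/(ln 0.5575)² = 92 events. With the two-stage O'Brien-Fleming boundary this becomes 92.7, rounded to 93 (plan 93).
- Mean event probability with exponential EFS and uniform accrual: (0.952 + 0.871)/2 = 0.911. Then 92.7/0.911 = 101.7, rounded to 102 (plan 102), and 102/0.85 = 120 (plan 120).

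So the exponential model agrees with the plan's own numbers.

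**4. Ceiling on the early-event share.** The monthly hazard is λ = −ln(EFS at 4 months)/4: control 0.229, experimental 0.128. The share with an event by time t is 1 − exp(−λt).

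| Time | Control | Experimental |
|---|---|---|
| Day 42 (1.380 months) | 27.1% | 16.2% |
| Day 22 (0.723 months) | 15.3% | 8.8% |

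At day 42 this is 13.8 and 8.2 of 51 per arm, or 22.1/93 = 24% of the planned events. On 60 enrolled per arm it is about 16 and 10. These counts include every event type, so they bound the exclusions from above. If 25% to 100% of early events are deaths or chemotherapy stops (an assumed range), the set loses about 4 to 16 controls and 2 to 10 experimental patients for this reason.

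**5. Effect on 4-month EFS.** Every patient removed has failed before month 4, so the per-protocol rate is the true rate divided by the share kept.

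- All events by day 42 removed: 0.40/0.729 = 55% and 0.60/0.838 = 72%.
- A quarter of them removed: 0.40/(1 − 0.25 × 0.271) = 43% and 0.60/(1 − 0.25 × 0.162) = 63%.
- All events by day 22 removed: 0.40/0.847 = 47% and 0.60/0.912 = 66%.

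**6. Effect on the hazard ratio.** This was simulated with 5,000 patients per arm, without censoring, removing every event by day 42. Under proportional hazards the HR was 0.55 in all patients and 0.54 in those kept. With a benefit confined to the first 42 days it was 0.87 and 0.98.

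**The case against.** A reader might infer that the set is selected on outcome rather than on deviations, that anyone with an early event is shut out, and that early harm or benefit of parenteral nutrition would be hidden. The article does not support this. Deviations are part of the definition. A nutritional stop or a QoL drop leaves chemotherapy and the questionnaires running, and scheduled imaging comes too late to exclude many progressions. Above all, ITT is the primary population, so the main test keeps every early event.

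The size is also open to challenge. The 27% and 16% spread the whole composite hazard evenly from day 0 and treat every event as an exclusion. Eligibility requires a life expectancy above 3 months and excludes PINI above 10 and recent weight loss above 2%, which should lower the early hazard. The conditions might be met by day 22. Under the proportional hazards behind the sample size the HR barely changes, and the early-effect scenario is only an illustration. Finally, minimum-exposure conditions are common in per-protocol sets, and the SAP, which is not shown, may deal with early events.

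Most of this stands, and it limits the point to early deaths and chemotherapy stops in one supporting analysis. It does not remove it. The two conditions are fixed in the article without an exemption, and on either reading of the timing some patients who followed the protocol are dropped because they reached the endpoint.

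**Conclusion.** The point holds in this limited form, and it is minor. As defined, the per-protocol analysis of EFS cannot isolate the impact of protocol deviations, because it also removes patients who died or stopped chemotherapy before about day 42 to 43 (day 22 at the earliest). EFS is overstated in both arms: at the extreme 55% and 72% at 4 months instead of 40% and 60%, and less in practice.

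The mechanism follows from the text alone. The size rests on the plan's EFS rates, a constant hazard and an unknown mix of event types, so 27% and 16% (or 15% and 9% by day 22) are ceilings and not estimates. The HR is nearly unchanged under proportional hazards and is at risk only if the effect is concentrated early. The ITT primary analysis, the sample size and the interim rule do not depend on this set.

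**What to change.** Keep the pre-specified deviation criteria and add one sentence: a patient with an EFS event before the first cycle was completed, or before the second post-baseline assessment was due, counts as meeting those two conditions. No patient is then excluded for having failed early, while patients who miss the conditions for other reasons still are. Defining the set by deviations only would also solve the problem, but giving up every minimum-exposure condition is more debatable. The same sentence should say what completes a cycle (the day-22 dose or day 42) and which assessments count.

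The cost is a short edit to the protocol or SAP with no new data. The article leaves the SAP open until database lock, so there is time to make it.

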#### Primary analysis

Stratification of patients regarding performance status prior to randomization may improve the power of the trial. For this reason the main analysis will be stratified by ECOG (stratum 1: PS < 2, stratum 2: PS ≥ 2) using the ITT population. A stratified log rank test will be used to compare the two treatment arms regarding the primary variable. The EFS-rates will be derived from the Kaplan Meier estimate and the confidence intervals will be calculated using Greenwood's formula. The above method relies on the assumption that events are recorded at the time they occur and there is no lag in the time at which they are reported. If this assumption is not satisfied, an alternative, interval censored analysis will be used.

#### Secondary analyses

A sensitivity analysis will be performed on the primary variable to assess the impact of protocol deviations using the per protocol analysis set.

The hazard ratio and the related 95% confidence interval (CI) for the experimental arm relative to control arm will be estimated by proportional hazard regression with treatment, centre and performance status as covariates.

OS, PFS, and TTP will be analyzed in the same manner as in the primary efficacy endpoint. Estimates of the ORR and 95% CI will be calculated and will be compared between treatment groups using the Cochran-Mantel-Haenszel (CMH) test adjusting by the stratification variables used in the stratified log rank test. For subjects with incomplete follow-up, time to last follow-up date will be used as the censoring time in the analysis of time-to-event data.

Descriptive statistics will be provided for the tumour-cachexia parameters. QoL scales, subscales and single item scores will be summarized by the mean and median for each arm and plotted by time. QoL data will be analysed using ANCOVA techniques. A logistic regression analysis will be carried out to identify relevant prognostic factors.

Incidence rates and 95% CI of Adverse Events (AEs) will be summarized. Subject disposition will be tabulated. Baseline characteristics, concomitant medications, vital signs and PS will be tabulated. Study drug administration and reasons for the deviations from the planned therapy will be tabulated. Summary tables will be prepared to examine the distribution of laboratory measures over time.

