## Background

Pancreatic cancer is an extremely aggressive malignancy characterized by extensive invasion, early metastasis, and marked cachexia. The yearly incidence of pancreatic cancer overlaps the mortality rate and the 5-year survival rate is less than 5% [1]. Subjects are afflicted with a variety of disconcerting symptoms, including profound cachexia and deterioration in performance status (PS), even when their tumour burden is low [2,3]. Therefore, one of the most important therapeutic targets is the improvement of quality of life (QoL) [4].

Cachexia is a strong independent predictor of mortality, poor therapeutic response, diminished functional capacity, and reduced QoL. It is defined as the debilitating state of involuntary weight loss, often connected with anorexia, tissue wasting, malnutrition, and inability for natural nutrition intake. The combination of these symptoms is also named "cancer anorexia-cachexia syndrome" [4]. The most important phenotypic feature is muscle wasting and functional impairment as a result of increased protein degradation and reduced protein synthesis or both [5]. In addition, it is a life-threatening and debilitating syndrome for 50% of all cancer subjects [5]. Compared to other solid tumours, the pancreatic cancer has the highest incidence for cancer cachexia (CC), as much as 80% at the time of diagnosis [4].

It has to be considered that the full effect of CC can not be identified by weight loss alone. Reduced food intake and systemic inflammation are also involved. Therefore, a multifactor cachexia profile was developed by the group of Bauer et al., based on weight loss, food intake and inflammatory status. These variables were investigated by determination of dietary intake, body composition, nutritional status, functional capacity and QoL in subjects with CC receiving chemotherapy [6].

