### Patient selection

PANUSCO focuses on hospitalised patients over 18 years of age suffering from advanced pancreatic adenocarcinoma with previous progression under chemotherapy.

Men and women over 18 years with histological confirmed advanced pancreatic adenocarcinoma which have received at least one previous chemotherapy (gemcitabine-based) will be screened for participation in the clinical trial. Patients will be contacted first-time by the (sub-) investigators at the outpatient's department. A detailed overview of recruitment criteria for inclusion and exclusion is given in table 1.

**Table 1 T1:** Eligibility Criteria

Inclusion criteria	Exclusion criteria
Written informed consent (IC)	Major surgery < 4 weeks prior to enrolment
Histological confirmed advanced pancreatic adenocarcinoma	Weight loss > 2% within the last seven days or caloric intake ≤ 500 kcal expected within the next five days
At least one previous chemotherapy (gemcitabine-based)	PINI-Index > 10
≥ 18 years old	Pregnancy or breastfeeding
Body weight ≥ 50 and ≤ 95 kg	> 4 weeks of parenteral nutrition within the last 6 months
BMI ≥ 19	Parenteral nutrition < 4 weeks prior to enrolment
Negative pregnancy test (females of childbearing potential)	Vulnerable populations (e. g. subjects incapable of giving consent personally)
Willingness to perform double-barrier contraception during study	Subject selection conflicts with warnings, precautions and contraindications stated for any investigational product
Expected life expectancy > 3 months	

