### Randomisation and standardised treatment scheme

All patients enrolled will be identifiable throughout the study. The investigator will maintain a personal list of patient numbers and patient names to enable records to be found at a later date. Upon inclusion each patient receives a unique identification number. After the patient's eligibility for randomisation has been assessed he/she will be randomly assigned to one of the two treatment arms (1:1) and receives a unique randomization number. The randomisation will be done and documented centrally and send by fax. Stratification will be performed prior to randomization by Eastern Cooperative Oncology Group Performance Status (ECOG PS) (stratum 1: PS < 2, stratum 2: PS ≥ 2). The randomisation list will be kept in safe and confidential custody at the involved CRO. The method of randomisation and the block sizes themselves will not be disclosed to the study sites, the monitors or any person involved in the clinical trial conduct. This information will be kept with the randomisation list.

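### The Cox model that supplies the hazard ratio omits baseline cachexia; adding baseline PINI, already measured at entry, would be a cheap, optional improvement

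*Protocol article*

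**What the plan says.** All references are to the protocol article.

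- **Secondary analyses** fixes the hazard-ratio model as "proportional hazard regression with treatment, centre and performance status as covariates". Tumour-cachexia parameters are otherwise to be described only.
- **Primary analysis** decides efficacy differently: "A stratified log rank test will be used to compare the two treatment arms regarding the primary variable". The strata are ECOG performance status below 2 and 2 or above.
- **Randomisation and standardised treatment scheme** uses the same single factor: "Stratification will be performed prior to randomization by Eastern Cooperative Oncology Group Performance Status (ECOG PS").
- **Background** states: "Cachexia is a strong independent predictor of mortality, poor therapeutic response, diminished functional capacity, and reduced QoL". The Discussion repeats this. The Background also describes a cachexia profile "based on weight loss, food intake and inflammatory status".
- **Patient selection, Table 1** excludes "PINI-Index > 10" and "Weight loss > 2% within the last seven days or caloric intake ≤ 500 kcal expected within the next five days". PINI, recent weight change and expected intake must therefore be assessed at entry.
- **Study objectives** uses "Prognostic Inflammatory and Nutritional Index (PINI) > 10" again, limited to patients without signs of acute inflammation, as one of three nutritional stopping criteria. Two of the three must be met, and withdrawal on the stopping criteria is part of event-free survival (EFS).

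**The concern.** The protocol justifies stratifying by performance status because this may improve power. The same reasoning applies to a factor that it calls a strong predictor, yet cachexia enters neither the allocation nor any stated model of the treatment effect. PINI is a candidate measure: it is available before treatment, it covers inflammation and nutrition, and it is linked to the endpoint, since a patient who enters just under 10 starts close to one of the stopping criteria.

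The Cox model is the only stated source of the hazard ratio and confidence interval, the effect size that readers will carry away. If an omitted baseline factor is prognostic, two things follow. The fitted hazard ratio moves towards 1, so the treatment term is less likely to reach significance. And a chance difference between the arms in that factor feeds straight into the estimate.

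**Working it through.** **1. The plan's own figures.** Inputs from Sample size estimation and Interim analysis: 4-month EFS of 60% and 40%, two-sided 0.05, power 0.80, 1:1 allocation, accrual 36 months, follow-up 4 months, 15% loss.

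- HR = ln(0.60)/ln(0.40) = 0.557.
- Schoenfeld, fixed design: 4 × (1.960 + 0.842)² / (ln 0.5575)² = 92.0 events.
- Two-stage O'Brien-Fleming with an interim at half the events: one-sided levels 0.0026 and 0.0240 (final critical value 1.977). Power is 79.7% with 92 events and 80.1% with 93.
- Event probabilities with exponential times and uniform accrual: 0.871 and 0.952, mean 0.911. 93/0.911 = 102 patients; 102/0.85 = 120 enrolled.

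Everything reproduces. These figures belong to the log-rank test, not to the Cox model.

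**2. Power of the Cox treatment term without and with the covariate.** The documents give no hazard ratio for PINI or for cachexia, so a range is assumed. Simulation: 102 patients, 36 + 4 months, marginal 4-month EFS held at 60% v 40%, four centres, 25% with performance status of 2 or above at an assumed HR of 1.5, a normally distributed baseline covariate, 3000 trials per row, rejection at |z| > 1.977.

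| Covariate HR per SD | Planned covariates | Covariate added | Gain (points) |
|---|---|---|---|
| 1.25 | 76% | 78% | 2 |
| 1.5 | 73% | 81% | 8 |
| 1.75 | 71% | 83% | 12 |
| 2.0 | 70% | 87% | 17 |

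A further run gave 79 v 81% at 1.25, 73 v 83% at 1.5 and 71 v 88% at 2.0, so the gain at 1.5 is about 8 to 10 points.

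**3. Sensitivity to the model.**

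- *Binary cachexia factor*, 50% prevalence, conditional treatment HR 0.557, performance status of 2 or above in 30%, rejection at |z| > 1.96. The SD of such a factor is 0.5, so HRs of 1.5, 2.0 and 3.0 equal 1.22, 1.41 and 1.73 per SD (square roots). Power is 75.1 v 76.9%, 71.4 v 76.7% and 63.3 v 76.5%. With no prognostic effect it is 76.8 v 76.4%, so a useless covariate costs about 0.4 points.
- *EFS built from repeated, noisy QoL forms plus competing events:* gain 0.5 to 2 points at 1.3 per SD, 5 to 7 at 1.6 and 9 at 2.0, smaller than in the table.

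**4. Where the gain comes from.** In the binary model the mean treatment HR is 0.569 without and 0.541 with the covariate at a cachexia HR of 2, and 0.600 v 0.542 at 3. The SD of the log HR does not fall (0.238 without, 0.243 with, at HR 2). With no treatment effect, rejection rates agree (5.8 to 5.9% without, 5.9 to 6.1% with). The gain is therefore less attenuation. It is not better precision, and type I error hardly changes.

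**5. Chance imbalance.** With 51 per arm, one standard error of the difference in a standardised covariate is √(4/102) = 0.198 SD. To first order the hazard ratio then shifts by a factor exp(0.198 × ln HR per SD): 1.045 at 1.25 and 1.084 at 1.5, or about 5% and 8%. For a binary factor with 30 to 50% prevalence, the chance of an arm difference of at least 10 percentage points is 27 to 31% at 102 patients and 23 to 27% at 120.

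**The case against.** **The power loss touches no planned decision.** This stands. Efficacy rests on the stratified log-rank test. The Cox model is secondary, has no power target and serves estimation. A reader might infer that the trial is underpowered or its primary test deficient; the documents do not support that, since the design figures reproduce and the proposed change leaves that test alone.

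**The planned hazard ratio is not biased.** A reader might take the attenuation for bias. It is largely non-collapsibility: adding a prognostic covariate changes which conditional hazard ratio is estimated. The planned estimate is valid for its own target, and chance imbalance under randomisation is part of what its confidence interval expresses. But that model is already conditional on centre and performance status, so one more baseline variable changes the estimand in degree, not in kind.

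**PINI is not cachexia.** This also stands. The protocol calls cachexia predictive, defines no single baseline variable for it and gives no strength for PINI. The stopping rule's limit to patients without acute inflammation shows that PINI can reflect other things. The entry limits on PINI, recent weight loss and BMI narrow the spread, so the low end of the range is plausible.

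**The QoL component may offset part of the effect.** EFS counts a change from baseline, and a cachectic patient may start lower with less room to fall. The smaller gains in the QoL-based simulation show that the size depends on how EFS is modelled. Performance status may carry part of cachexia's effect, but the gain persisted in simulation when the two were correlated.

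**Centre plus the stratification factor is a defensible set, and details are left to the SAP.** True in general, but the article names the covariates, so this is a stated choice and can be commented on.

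**Conclusion.** The stated model leaves out a baseline measure that the protocol's own rationale suggests is prognostic and that is already collected. Adding it is a cheap improvement to a secondary estimate. It is optional and does not correct an error.

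The size rests on an assumed prognostic strength: about 0 to 2 power points for the Cox treatment term at up to about 1.25 per SD, and about 8 to 10 at 1.5 per SD under proportional hazards, with smaller gains when EFS is built from QoL forms. Nothing in the documents shows which value applies. Nor would adjustment remove attenuation and chance imbalance altogether: PINI is a proxy for cachexia, so both are reduced only as far as it carries prognostic information.

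**What to change.** Keep the ECOG-stratified log-rank test as the primary analysis. In the SAP, before the interim analysis, specify baseline log PINI as one continuous covariate, with centre and performance status, in the secondary Cox models for EFS, OS and PFS. Report the hazard ratio with the currently planned covariates alongside, so that readers can see what the adjustment does.

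The cost is one line in the SAP and no new data. The model spends one more degree of freedom against about 93 events, and the adjusted hazard ratio is conditional on one more baseline variable.
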